### Severity Grade Description

|          |   |                                                                                                |
|----------|---|------------------------------------------------------------------------------------------------|
| Mild     | 1 | Symptoms causing no or minimal interference with usual social and functional activities        |
| Moderate | 2 | Symptoms causing greater than minimal interference with usual social and functional activities |
| Severe   | 3 | Symptoms causing inability to perform usual social and functional activities                   |

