## 7. ASSESSMENT OF SAFETY

### 7.1 Safety Parameters: Methods and Timing for Assessing, Recording and Analysing

During the trial, ~~approximately 330 mL~~~~not more than 200 mL~~ of blood (~~excluding repeat and re-screen samples~~~~excluding repeat samples~~) for each subject will be sampled at the time points indicated in the programmed activities; includes safety laboratory samples, immunogenicity testing and plasma for assessing the HIV viral load and CD4 levels (~~Figure 19~~~~Figure 19~~).

The samples will be properly labelled and sent to the central laboratories as soon as possible. The investigators will review the laboratory report, document this review, and record any clinically relevant changes that occur during the trial in the AE section of the CRF. The following safety and tolerability evaluations will be performed:

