## **7.2 Procedures for Eliciting Reports of and for Recording and Reporting Adverse Event and Intercurrent Illnesses**

The original terms used in the CRFs by investigators to identify AEs will be coded using the Medical Dictionary for Regulatory Activities (MedDRA). Special attention will be given to those subjects who have discontinued treatment due to an AE or who experienced a severe or a serious AE.

The present clinical trial will be conducted in accordance to Standard Operating Procedures (SOPs) in conformity with regulatory requirements worldwide to ensure appropriate reporting of safety information. Adverse events will be reported from the time the subject signs the informed consent form until the subject completes the last trial procedure.

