### **7.2.1 Adverse Event Definitions and Classifications**

#### **Adverse Event**

An AE, as defined by the International Conference on Harmonisation (ICH), is any untoward medical occurrence in a clinical trial subject administered a pharmaceutical product. An AE does not necessarily have a causal relationship with the treatment. An AE can therefore be any unfavorable and unintended sign (including an abnormal laboratory finding), symptom, or disease temporally associated with the use of a medicinal (investigational) product, whether or not related to the medicinal (investigational) product.

This includes any occurrence that is new in onset or aggravated in severity or frequency from the baseline condition, or abnormal results of diagnostic procedures, including laboratory test abnormalities.

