### **Serious Adverse Event**

A SAE as defined by ICH is any untoward medical occurrence that at any dose meets any of the following conditions:

- results in death,
- is life-threatening; i.e., the subject was at risk of death at the time of the event; this does not refer to an event that hypothetically might have caused death if it were more severe,
- requires inpatient hospitalization or prolongation of existing hospitalization,
- results in persistent or significant disability/incapacity or
- there is a congenital anomaly/birth defect.

Note: Medical and scientific judgment should determine whether an adverse event should be classified as serious in other situations. Adverse events classified as serious may include important medical events that are not immediately life threatening or could result in death or hospitalization but may jeopardize the subject or require intervention to prevent one of the outcomes listed above. Any AE is considered a SAE if it is associated with clinical signs or symptoms judged by the investigator to have a significant clinical impact.

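### The only adverse event severity scale grades by symptoms, so an abnormality without symptoms has no grade, or is mild by default, and can never be severe

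*Protocol*

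**What the plan says.** Section 7.2.1 of the protocol defines an AE to include "any unfavorable and unintended sign (including an abnormal laboratory finding), symptom, or disease" and also "abnormal results of diagnostic procedures, including laboratory test abnormalities". Section 7.1 has the investigator review each laboratory report and "record any clinically relevant changes that occur during the trial in the AE section of the CRF". Abnormalities without symptoms are therefore meant to be recorded as AEs once they are judged clinically relevant.

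The severity table in Section 7.2.1 (Severity Grade Description) has three grades. The lowest, called mild, is worded "Symptoms causing no or minimal interference with usual social and functional activities". The top grade, called severe, is reserved for "Symptoms causing inability to perform usual social and functional activities". The middle grade follows the same pattern: it too starts from symptoms, and asks for interference above the minimal level.

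Section 7.2 then gives the severe grade a use: "Special attention will be given to those subjects who have discontinued treatment due to an AE or who experienced a severe or a serious AE".

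Section 3.1 makes safety and tolerability the primary endpoint. It names laboratory tests among the components, with CD4 counts and viral load for HIV-positive subjects. Section 7.1 adds a thoracic CT before the first inoculation and four weeks after the second, to assess change in hilar node size.

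**The concern.** The AE definition admits events that the severity scale cannot grade. Several of the signals this trial looks for can be silent. Every subject takes isoniazid for a month, and AST and ALT should be normal at entry (Section 4.2, criterion 1), so a marked rise would have developed on trial. The synopsis says that CT is done to detect a Koch reaction at the hilar nodes, which need not cause symptoms. A CD4 fall is a laboratory finding.

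If severity follows symptoms alone, the size of such findings is lost from the AE record, and the severe flag cannot pick them up. Investigators at the three sites may also handle the gap differently: one may leave the grade blank, another may enter mild, and a third may improvise a grade from the laboratory value.

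**Working it through.** The protocol states no figure on this point, so the check sets its sections side by side.

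1. **Is a finding without symptoms an AE?** Yes. Section 7.2.1 includes abnormal laboratory findings and diagnostic results, and Section 7.1 sends clinically relevant laboratory changes to the AE pages.

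2. **Which grade does it get?** All three definitions begin with symptoms, and only the degree of interference with usual activities changes. Read strictly, an event without symptoms meets none of them. Read loosely, it causes no interference, and grade 1 is the nearest fit. On either reading grades 2 and 3 are closed to it. As an illustration, ALT at 2 times and at 15 times the upper limit of normal, both without symptoms, could not be told apart by grade.

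3. **Is there another scale?** Section 7.1 has a 0 to 3 scale, but only for redness, swelling and induration at the injection site; pain has a visual analogue scale. The protocol grades no laboratory, CD4, viral load or CT finding by size.

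4. **What depends on the grade?** The only stated use is the special attention in Section 7.2, which applies if an AE is severe, or is serious, or led to discontinuation of treatment. The first of these three routes is closed to an event without symptoms.

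5. **Is size reported elsewhere?** Section 9.3.1 gives two answers:
   - Laboratory parameters are listed and summarised by group and visit, as absolute values and as change from baseline.
   - Chest CT, CD4 count and viral load results are listed, with no group summary stated.

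   Section 3.1 counts CD4 and viral load among the laboratory tests, so they could be taken as covered by the first rule. The specific sentence in Section 9.3.1 points to listing only.

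6. **How often could it arise?** Figure 19 gives the number of assessments after screening:
   - General laboratory sampling on Days 21, 28, 35, 49, 56, 63 and 84: 7 × 96 subjects = 672 panels.
   - CD4 count, and likewise viral load, on Days 28, 35, 63 and 84: 4 × 48 HIV-positive subjects = 192 of each.
   - CT on Days 28 and 84: one change in node size per subject, at most 96.

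   These are occasions on which an ungradable AE could appear. They are not counts of such AEs, because only clinically relevant changes are recorded as AEs and the protocol gives no rate for them.

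**The case against.** The strongest reply is that AE severity is not the only place where size is recorded. Laboratory tests are a component of the primary endpoint in their own right, and their changes from baseline are summarised, so the two ALT values above would differ in the safety tables. That stands for chemistry and haematology. It does not stand for CD4, viral load and CT, which are only listed.

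A second reply is that a large silent abnormality can still be flagged. The important-medical-event note under Serious Adverse Event requires no symptoms, significant abnormalities are followed up (Sections 7.1 and 7.3), and the safety monitoring committee sees unblinded results (Sections 3.6 and 9.4). This is correct and limits the harm. But each of these routes works outside the severity grade and leaves the gap in the scale as it is.

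A third reply is that a toxicity table may sit in the analysis plan or the CRF guidelines, which are not shown. The protocol refers to none. An analysis plan could add shift tables, but investigators assign grades during the trial under the protocol's definitions, and a later analysis would not correct what they recorded.

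A reader might also infer four stronger things that the text does not support:

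- *That such findings must be graded mild.* The table does not say so; mild is a likely default.
- *That dose groups will be compared on faulty grades.* Section 9.3.1 summarises AEs by system organ class and preferred term, and specifies no comparison of grades.
- *That the closing sentence on seriousness turns ordinary symptomatic AEs into serious ones.* It reads "Any AE is considered a SAE if it is associated with clinical signs or symptoms judged by the investigator to have a significant clinical impact". It requires the investigator to judge the impact significant, so an ordinary AE does not qualify. The threshold is undefined and broad, but deleting the sentence would narrow the capture of serious events. That is a debatable trade-off, and deletion is not proposed here.
- *That classification as serious drives unblinding.* Section 3.3 gives a serious AE only as an example of premature unblinding to be documented. Section 3.8 ties code breaking to a medical emergency in which the assignment is needed for treatment decisions, or to a suspected unexpected serious adverse reaction.

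**Conclusion.** The point holds as a gap in the severity scale. The protocol defines AEs that its only AE severity scale cannot grade by size. An abnormality without symptoms is ungradable, or mild by default, and cannot be severe.

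The consequence is moderate. It is small for chemistry and haematology. It is larger for CD4 count, viral load and hilar node size, where neither a grade nor a planned group summary conveys magnitude. The number of affected events cannot be derived from the protocol.

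The conclusion assumes that no separate grading table, unmentioned in the protocol, is in force, and that Section 9.3.1 means what it says in listing CT, CD4 and viral load. Because the gap lies within the primary safety endpoint and is cheap to close, it should be closed.

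**What to change.** In Section 7.2.1, Severity Grade Description:

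- State that the interference scale applies to AEs with symptoms.
- Grade laboratory and CD4 AEs by magnitude from a pre-specified toxicity table, for example multiples of the limits of normal for laboratory tests and absolute or percentage change for CD4.
- Grade CT findings by measured change in hilar node size.
- State how an event with both symptoms and a measured abnormality is graded.

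This changes only the wording of the protocol and the CRF guidelines. The laboratory values and scans are already scheduled, so no new data are needed, and no treatment rule is touched. The cost is slightly more grading work at the sites. Some events will also be graded more severe than under the present wording, so more subjects may fall under the special attention of Section 7.2.

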**Outcome**

Each adverse event will be characterized according to the outcomes:

| Outcome         | Description                                                                                                              |
|------------------------|---------------------------------------------------------------------------------------------------------------------------------|
| Resolved               | The subject has fully recovered from the event with no observable residual effects.                                             |
| Improved               | The effects of the event are improving but have not returned to baseline.                                                       |
| Persisting             | The effects of the event are still present and changing (may be worsening). The event is not considered stabilized or resolved. |
| Resolved with sequelae | The subject has fully recovered from the event with some observable residual effects.                                           |
| Fatal                  | The event was the primary cause of death (may or may not be the immediate cause of death).                                      |
| Unknown                | The event outcome is unknown.                                                                                                   |

Death is an outcome of an event and not an event per se. However, sudden death or death due to unexplainable cause(s) is to be reported as an adverse event, but follow-up will be pursued until cause of death is determined.

**Action Taken with Drug (INH and RUTI ® placebo)**

Action taken with study drug in relation to each adverse event will be characterized as follows:

- Drug withdrawn [i.e., study drug(s) discontinued permanently]
- Drug withheld [e.g., study drug(s) not administered for 1 dosing visit or period of time]
- Unknown
- None

**7.2.2 Adverse Event Reporting Procedures****All Adverse Events**

All AEs will be reported from the time a signed and dated informed consent form is obtained until completion of the last trial-related procedure. The AEs meeting the definition of SAEs must

be reported using the SAE Form (see Serious Adverse Events below), including SAEs spontaneously reported to the investigator within 30 days after the subject has completed the trial (including post-trial follow-up). The sponsor will evaluate any safety information that is spontaneously reported by an investigator beyond the time frame specified in the protocol.

All AEs that meet the definition of a SAE will be reported as SAEs, regardless of whether they are protocol-specific measurements.

All AEs, regardless of seriousness, severity, or presumed relationship to trial drug, must be recorded using medical terminology in the source documents and the CRF. Whenever possible, diagnoses should be given when signs and symptoms are due to a common aetiology (e.g., cough, runny nose, sneezing, sore throat, and head congestion should be reported as “upper respiratory infection”). Investigators must record their opinion concerning the relationship of the AE to trial drug in the CRF. All measures required for AE management must be recorded in the source documents and reported according to sponsor instructions.

The sponsor assumes responsibility for appropriate reporting of AEs to the regulatory authorities. The sponsor will also report all SAEs that are unlisted and associated with the use of the drug to the investigator. The investigator (or sponsor where required) must report these SAEs to the appropriate Independent Ethics Committee/Institutional Review Board (IEC/IRB) that approved the protocol unless otherwise required and documented by the IEC/IRB.

Subjects must be provided with a “trial card” indicating the name of the investigational product, the trial number, the investigator’s name, a 24 hour emergency contact number, and, if applicable, excluded concomitant medications.

### **Serious Adverse Events**

All SAEs occurring during the clinical trial must be reported to the appropriate sponsor contact person by investigational staff within 24 hours of their knowledge of the event.

Information regarding SAEs will be transmitted to the sponsor using the SAE Form, which must be signed by a physician on the investigational staff. The initial report of a SAE should be done by fax. If necessary, it may be done by telephone. Subsequent to a telephone report of a SAE, the signed SAE Form must be completed and transmitted to the sponsor within one working day.

### 7.3 Type and Duration of the Follow-up of Subjects after Adverse Events

Any clinically significant abnormalities or AEs detected during the trial or not resolved upon discontinuation of the subject's participation in the trial, or by the end of the trial, must be followed up until any of the following occurs:

- the event resolves
- the event stabilizes
- the event returns to baseline, if a baseline value is available
- the event can be attributed to agents other than the trial drug or to factors unrelated to trial conduct
- when it becomes unlikely that any additional information can be obtained (subject or health care practitioner refusal to provide additional information, lost to follow-up after demonstration of due diligence with follow-up efforts)

#### Pregnancy

Pregnancy alone is not considered an adverse event. However, any report of pregnancy that occurs in a female subject within 1 month after the end of visit, even if the subject is withdrawn from study, must be reported on the Pregnancy Form. The investigator must follow the pregnancy either to termination or to term and will collect data on both maternal and fetal outcome. All pregnancy outcomes will be recorded on the Pregnancy Form.

Normal outcomes will be communicated to the Sponsor within 30 calendar days of birth/delivery. Abnormal pregnancy outcomes and/or any adverse event for the child or fetus (including miscarriage), will also be recorded in the adverse event CRF and on the SAE form. The associated SAE form should be sent to the Sponsor. An adverse event CRF and SAE form as appropriate will be completed if the subject sustains an event.

#### Overdose

Overdose is defined as anything outside the defined or prescribed use as applicable for the study drug and trial design. Occurrences of overdose should be reported to the Sponsor for tracking purposes. Additional instructions for reporting overdose information will be provided by the Sponsor at the time of notification.

## 8. ACTIVE TB SURVEILLANCE [9, 10, 11]

### 8.1 Diagnosis of Pulmonary TB

#### 8.1.1 Clinical Features

Accordingly with the WHO Clinical Manual for HIV and TB, the most important symptoms in the diagnosis of pulmonary TB (PTB) are the following:

- Cough for more than 2 or 3 weeks
- Sputum production
- Weight loss

Patients with PTB may also have other symptoms. These may be respiratory or constitutional (general or systemic).

Respiratory: chest pain, haemoptysis, breathlessness

Constitutional: fever, night sweats, tiredness, loss of appetite, secondary amenorrhoea.

Weight loss and fever are more common in HIV+ PTB patients than in those who are HIV-. Conversely, cough and haemoptysis are less common in HIV+ PTB patients than in those who are HIV-. This is probably because there is less cavitation, inflammation and endobronchial irritation in HIV+ patients.

Therefore, a PTB suspect is a patient with a cough for more than 2 to 3 weeks, and must submit sputum samples for smear microscopy and mycobacterial culturing.

#### 8.1.2 Chest X-Ray in Diagnosis

No chest X-ray (CXR) pattern is absolutely typical of PTB, especially with underlying HIV infection. The table below (Table 7) shows so-called “classical” and “atypical” CXR patterns. The classical pattern is more common in HIV- patients, and the atypical pattern in HIV+ patient.

**Table 7 “Classical” and “atypical” chest X-ray patterns**

| CLASSICAL PATTERN                | ATYPICAL PATTERN                                  |
|----------------------------------|---------------------------------------------------|
| Upper lobe infiltrates           | Interstitial infiltrates (especially lower zones) |
| Bilateral infiltrates            | Intrathoracic lymphadenopathy                     |
| Cavitation                       | No cavitation                                     |
| Pulmonary fibrosis and shrinkage | No abnormalities                                  |

### 8.1.3 Confirmatory Diagnosis by Smear Microscopy and Mycobacterial Culturing

A PTB suspect should submit three sputum samples. Secretions build up in the airways overnight. So an early morning sputum sample is more likely to contain TB bacilli than one taken later in the day. It may be difficult for an outpatient to provide three early morning sputum samples. Therefore sputum samples will be provided as follows:

|       |          |                                                                                                                                                                                                                   |
|-------|----------|-------------------------------------------------------------------------------------------------------------------------------------------------------------------------------------------------------------------|
| Day 1 | Sample 1 | Patient provides an “on-the-spot” sample under supervision when presenting to the health facility. A sputum container will be given to the patient to take home for an early morning sample the following morning |
| Day 2 | Sample 2 | Patient brings an early morning sample                                                                                                                                                                            |
|       | Sample 3 | Patient provides another “on-the-spot” sample under supervision                                                                                                                                                   |

Specimens will be first processed to remove viable organisms other than mycobacteria through a specific decontamination process. Smear examination and liquid culturing will be done. *Mycobacterium tuberculosis* complex identification and sensitivity testing will be ensured through specific molecular biology testing.

## 8.2 Diagnosis of Extrapulmonary TB

Extrapulmonary (EPTB) can occur at any age. HIV+ adults are particularly susceptible. Up to 25% of TB cases may present with EPTB. The common forms of EPTB associated with HIV are the following: lymphadenopathy, pleural effusion, pericardial disease, miliary TB, and meningitis. Many patients with EPTB also have coexistent pulmonary TB.

Definitive diagnosis of EPTB is often difficult. Diagnosis may be presumptive, after exclusion of other conditions. Patients usually present with constitutional features (fever, night sweats, weight loss) and local features related to the site. The certainty of diagnosis will depend of the diagnostic tools including image devices and organ sampling. Thus lymphadenopathy will require lymph node needle aspirate or biopsy for cytology/histology and mycobacterial stain and culturing; miliary TB will require CXR and mycobacterial stain and culturing of sputum, cerebrospinal fluid, bone marrow, liver or blood; Pericardial disease would require CXR, ECG, Echocardiography and pericardiocentesis, also to be stained and cultured; Pleural disease, would require CXR, pleural aspiration and pleural biopsy, etc.

